## Abstract

**Introduction:**

Over one-quarter of children in sub-Saharan Africa are stunted; however, commercial supplements only partially meet child nutrient requirements, cannot be sustainably produced, and do not resolve physiological barriers to adequate nutrition (eg, inflammation, microbiome dysbiosis and metabolic dysfunction). Redesigning current infant and young child feeding (IYCF) interventions using locally available foods to improve intake, uptake and utilisation of nutrients could ameliorate underlying pathogenic pathways and improve infant growth during the critical period of complementary feeding, to reduce the global burden of stunting.

**Methods and analysis:**

Child Health Agriculture Integrated Nutrition is an open-label, individual household randomised trial comparing the effects of IYCF versus ‘IYCF-plus’ on nutrient intake during infancy. The IYCF intervention comprises behaviour change modules to promote infant nutrition delivered by community health workers, plus small-quantity lipid-based nutrient supplements from 6 to 12 months of age which previously reduced stunting at 18 months of age by ~20% in rural Zimbabwe. The ‘IYCF-plus’ intervention provides these components plus powdered NUA-45 biofortified sugar beans, whole egg powder, moringa leaf powder and provitamin A maize. The trial will enrol 192 infants between 5 and 6 months of age in Shurugwi district, Zimbabwe. Research nurses will collect data plus blood, urine and stool samples at baseline (5–6 months of age) and endline (9–11 months of age). The primary outcome is energy intake, measured by multipass 24-hour dietary recall at 9–11 months of age. Secondary outcomes include nutrient intake, anthropometry and haemoglobin concentration. Nested laboratory substudies will evaluate the gut microbiome, environmental enteric dysfunction, metabolic phenotypes and innate immune function. Qualitative substudies will explore the acceptability and feasibility of the IYCF-plus intervention among participants and community stakeholders, and the effects of migration on food production and consumption.

**Ethics and dissemination:**

This trial is registered at ClinicalTrials.gov (NCT04874688) and was approved by the Medical Research Council of Zimbabwe (MRCZ/A/2679) with the final version 1.4 approved on 20 August 2021, following additional amendments. Dissemination of trial results will be conducted through the Community Engagement Advisory Board in the study district and through national-level platforms.

**Trial registration number:**

NCT04874688.

STRENGTHS AND LIMITATIONS OF THIS STUDYIndividually randomised trial to demonstrate impact of a new proposed infant and young child feeding (IYCF) and behaviour change intervention.Community-based study using local nutrient-dense foods conducted in a rural Zimbabwean community.Improved IYCF practices promoted through a behaviour change strategy at the onset of complementary feeding period between 5 and 6 months.Measurement of a broad range of biomarkers including dietary intake, anthropometry and laboratory assays.Limitation of a short follow-up period to measure outcomes.

## Introduction

Undernutrition underlies 45% of child deaths among children <5 years^1^. Linear growth failure in childhood is the most prevalent form of undernutrition globally. An estimated 149 million children under 5 years of age are stunted, with a length-for-age Z-score (LAZ) more than 2 SD below the population median.^2^ Stunting affects almost one-third of children in sub-Saharan Africa, leading to reduced human capacity and increased long-term risk of chronic disease; it is therefore a surrogate marker of child health inequalities.^1^

The period from 6 to 24 months of age is one of the most critical phases of linear growth,^3^ when stunting prevalence peaks due to high demand for nutrients coupled with limited quality and quantity of complementary foods.^2^ Infant diets in rural sub-Saharan Africa often have low dietary diversity and a heavy reliance on white maize, which is high in starch and low in other nutrients. Interventions to improve infant and young child feeding (IYCF) typically include nutrition counselling to caregivers, plus a combination of commercial and locally available food products with or without micronutrients. However, a meta-analysis^4^ of 42 studies showed only a modest impact of complementary feeding interventions on linear growth. Small-quantity lipid-based nutrient supplements (SQ-LNS), which are micronutrient-fortified ready-to-use products, show a small but measurable impact on LAZ.

We recently conducted the Sanitation Hygiene Infant Nutrition Efficacy (SHINE) trial,^5^ a 2×2 factorial cluster-randomised trial of improved water, sanitation and hygiene and improved IYCF in rural Zimbabwe. A combination of IYCF messages and provision of SQ-LNS between 6 and 18 months of age improved LAZ of children at age 18 months by+ 0.16 (95% CI 0.08 to 0.23) and reduced stunting by 20%.^5^ The intervention also increased haemoglobin by 2.0 g/L (95% CI 1.3 to 2.8) and reduced anaemia by almost 25%.^5^ However, despite this intensive IYCF intervention, 32%, 73% and 23% of infants did not meet energy, folate and zinc/iron dietary intake requirements, respectively, as determined by 24-hour recall in a subgroup at 12 months and over one-quarter remained stunted. We also found evidence for barriers to infant nutrition, including caregiver capabilities,^6^ household characteristics,^5^ infant enteropathogen carriage,^7^ and systemic and intestinal inflammation,^8 9^ which were not resolved by the IYCF intervention.^10^ Thus, we believe that persistent barriers to nutrient intake, uptake and utilisation limited the impact of the IYCF intervention.

Nutrient intake is influenced by food insecurity, household purchasing power and women’s disempowerment to make decisions about land use, crop choice and distribution of food within the household; and inequitable gender beliefs.^5 11^ Nutrient uptake and utilisation are influenced by intestinal pathologies which are highly prevalent among children in low-resource settings.^3^ First, environmental enteric dysfunction (EED), a subclinical pathology of the small intestine characterised by intestinal inflammation and blunted villi, may impair efficient intestinal uptake of nutrients. Second, disturbance of the normal assembly of the gut microbiota may impair its roles in immune maturation, intestinal development and nutrient metabolism, thereby impairing growth.^12^ Third, systemic inflammation arising from gut pathology increases energy requirements, reduces circulating micronutrients and inhibits the growth hormone axis.^13^ Previously, barriers to intake, uptake and utilisation of nutrients have largely been addressed in isolation; however, addressing these in parallel could ultimately improve growth and development in young children. Here, we present methodology for the Child Health Agriculture Integrated Nutrition (CHAIN) trial, which aims to address each of these barriers together through a randomised IYCF intervention.

## Study overview

CHAIN is an open-label, individually randomised household trial comparing the effects of IYCF versus an enhanced IYCF intervention (‘IYCF-plus’) on energy and nutrient intake, growth and haemoglobin in infants at high risk of stunting. The trial was completed in February 2022 while the trial design paper was under review. The overarching goal of this trial is to fill key nutrient gaps among infants in rural sub-Saharan Africa through an improved IYCF intervention using locally available foods that could ultimately be sustainable through agriculture. A total of 192 rural Zimbabwean children were enrolled in the trial between 5 and 6 months of age; interventions were delivered from 6 to 12 months of age and the primary endline outcome of energy intake was assessed at 9 months of age (window 9–11 months). Interventions continued to be delivered until 12 months of age regardless of whether the endline visit was already completed, and all children were followed for endline visits to obtain the primary outcome. Our approach builds on the SHINE IYCF package, which reduced stunting but did not close all nutrient gaps.^5^ We expect the CHAIN population will be similar to the SHINE population described above, as they are from the same rural community. CHAIN will test the impact of additional foods (powdered NUA-45 bio-fortified sugar beans, whole egg powder, moringa leaf powder and provitamin A (PVA) maize) that are nutrient-rich, culturally acceptable, locally sustainable and may have functional properties to ameliorate underlying pathogenic pathways, thereby tackling the identified barriers to nutrient intake, uptake and utilisation. For the duration of the trial, these foods were provided by community health workers (CHWs) as dried powders, which can be added to infant porridge as point-of-use fortificants. However, if shown to be efficacious, this trial would provide strong proof-of-principle that a comprehensive improvement to complementary feeding using locally available foods can substantially improve child nutrition. The chosen intervention foods have potential for local communities ultimately to become self-sufficient through modifications and adaptations to local agricultural systems that include local production and processing of these foods.

## Study objectives

### Objective 1

Evaluate the effect of an enhanced infant feeding intervention (‘IYCF-plus’) on energy intake at 9 months of age (window 9–11 months) in a randomised, community-based trial in rural Zimbabwe. We hypothesise that provision of powdered fortificants (PVA maize, NUA45 sugar beans, moringa and egg) for infants from 6 months of age will provide more energy at 9 months of age than the current standard-of-care IYCF intervention (trial primary outcome).

### Objective 2

Evaluate the impact of IYCF-plus on nutrient intake, growth and haemoglobin at 9 months of age (window 9–11 months) in a randomised, community-based trial in rural Zimbabwe. We hypothesise that IYCF-plus will improve the intake of key nutrients (protein, iron, zinc and folate) in 9-month-old infants compared with the standard-of-care IYCF intervention, and that IYCF-plus will increase length-for-age, weight-for-age, weight-for-length and haemoglobin more than IYCF (all secondary outcomes).

### Objective 3

Evaluate the impact of IYCF-plus on biological barriers to nutrient uptake and utilisation at 9 months of age (window 9–11 months) in a randomised, community-based trial in rural Zimbabwe. We hypothesise that the IYCF-plus intervention will increase microbiota maturity, ameliorate EED, reduce systemic inflammation and improve innate immune function in children aged 9 months, compared with the standard-of-care IYCF intervention.

### Objective 4

Identify metabolic signatures of the IYCF-plus intervention in young children at 9 months of age (window 9–11 months) in a randomised, community-based trial in rural Zimbabwe. We hypothesise that the IYCF-plus intervention will increase the concentrations of essential amino acids and choline at 9 months of age more than the standard-of-care IYCF intervention.

### Objective 5

Explore the acceptability and feasibility of the IYCF-plus intervention among participants and community stakeholders using qualitative methodology. Information from this assessment will be shared with policy makers to help design a larger roll-out of this intervention at district, provincial or national level.

### Objective 6

Explore the extent to which women’s empowerment influences IYCF practices and nutrition outcomes in rural smallholder agricultural households.

We hypothesise that infants of women scoring in the highest tertile of the Women’s Empowerment Agriculture Index (WEAI) will have improved macronutrient and micronutrient intake compared with infants of women in the lowest tertile of the WEAI index.

### Objective 7

Identify the extent of regional and international migration and movement (both rural–rural and rural–urban) at the household level, explore the type, frequency and impact of any associated remittance flows on food consumption and production, and consider the importance of migration to any changes in established food cultures. Information from this assessment will be shared with policy makers to help design a larger roll-out of this intervention at district, provincial or national level.

## Rationale for interventions

The CHAIN trial will compare IYCF as tested in the SHINE trial^5^ vs an enhanced IYCF intervention (‘IYCF-plus’). IYCF comprises a set of sequential behaviour change modules focusing on improved IYCF practices (eg, nutrient density, feeding during illness and dietary diversity), together with provision of daily SQ-LNS from 6 to 12 months of age, and powdered maize to make infant porridge. IYCF-plus comprises all the components of the IYCF intervention, plus four additional food supplements: PVA maize, NUA-45 sugar beans, moringa leaf powder and whole egg powder. We have chosen this combination of ‘functional’ food supplements to close the remaining nutrient gaps for young children identified during SHINE (table 1) and to ameliorate pathogenic pathways that impede uptake and utilisation of nutrients.

**Table 1 T1:** Nutrient provision in IYCF and IYCF-plus trial arms

Figure 1. Nutrient requirements from complementary food and provided by IYCF and IYCF-PLUS intervention diets with and without estimated mealie meal consumption for three age groups of children. Red (fails to meet requirement), orange (meets >88% requirement), green (exceeds requirement).*

6–8 months				9–11 months			12–24 months		
Nutrient	Required from complementary food	IYCF	IYCF-PLUS	Required from complementary food	IYCF	IYCF-PLUS	Required from complementary food	IYCF	IYCF-PLUS
Energy (kcal) from supplement alone	270	**118**	**222**	451	**118**	**247**	746	**118**	**272**
Energy (kcal) from supplement+estimated mealie meal intake		**243**	**347**		**368**	**497**		**618**	**772**
Protein (g)	7.7	**2.6**	**10.8**	8.1	**2.6**	**12.6**	8.1	**2.6**	**14.4**
Fat (g)	0.8	**9.6**	**15.7**	7.6	**9.6**	**15.8**	18.0	**9.6**	**16.0**
Vitamin A (µg RE)	207	**400**	**519**	222	**400**	**540**	238	**400**	**560**
Folic acid (µg)	48	**80**	**132**	50	**80**	**160**	133	**80**	**188**
Calcium (mg)	232	**280**	**375**	246	**280**	**438**	360	**280**	**502**
Iron (mg)	9.2	**6.0**	**9.0**	9.2	**6.0**	**10.4**	5.7	**6.0**	**11.9**
Zinc (mg)	3.8	**8.0**	**9.1**	3.9	**8.0**	**9.5**	3.8	**8.0**	**9.8**
Choline (mg)	47	**13**	**145**	55	**13**	**152**	114	**13**	**158**

*Nutrient requirements from complementary food calculated as total requirement less provided in breastmilk. Estimated mealie meal consumption is 125 kcal, 250 kcal, and 500 kcal based on observed intakes during SHINE trial. IYCF diet includes SHINE IYCF behaviour change modules +20 g Nutributter per day. IYCF-PLUS diet includes IYCF behaviour change modules +20 g Nutributter per day+whole egg powder, moringa powder, and iron and zinc-fortified sugar bean powder.

IYCF, infant and young child feeding; SHINE, Sanitation Hygiene Infant Nutrition Efficacy.

**Figure 1 F1:**
[figure not shown]
Hypothesised impact of IYCF-plus intervention on barriers to nutrient intake, uptake and utilisation for healthy child growth. IYCF, infant and young child feeding.

PVA Maize is a biofortified maize rich in beta-carotenes, which is grown in Zimbabwe. Studies in neighbouring countries have shown that daily intake of PVA maize can improve the vitamin A status of children.^14–18^ PVA maize appears less prone to contamination with aflatoxin, which is a fungal toxin affecting agricultural crops during growth, storage and processing that may impair child growth.^19^

NUA45 sugar beans are a high-nutrient bean variety providing bio-fortified zinc and iron, a high-protein efficiency ratio, plus folate and resistant starch. Biofortified beans significantly increased haemoglobin, serum ferritin and body iron in African populations including Rwandan women.^20–23^

Moringa oleifera is a widespread crop in Zimbabwe. Dried moringa leaves can be ground into a powder providing a rich source of protein, fibre, mineral and micronutrients, including vitamin A, calcium, folate, vitamin C and vitamin E, and antioxidant polyphenols. Moringa leaf powder is available in shops in Zimbabwe as a food supplement. Pilot studies show that moringa leaf powder is safe and widely accepted as a dietary supplement by children and caregivers in sub-Saharan Africa,^24 25^ but there have been no randomised trials.

Whole egg powder is commercially available, easily reconstituted and retains the nutrient content of whole eggs. Egg production is common in rural Zimbabwe. One egg per day for 6 months to children between 6–15 months of age increased LAZ by 0.63 in Ecuador.^26^ This large effect is likely attributable to high-quality protein and choline, which are critical nutrients for linear growth.^27 28^ Eggs contain all nine essential amino acids in proportions that closely match infant requirements for organ and muscle mass accretion. Choline is an essential nutrient that promotes growth in animal models.^29^ Children with EED have reduced circulating concentrations of phosphatidylcholines,^30^ which are required for chondrogenesis at the growth plate, and reliant on adequate dietary intake of choline. One egg meets the majority of an infant’s daily requirement. Eggs are also high in fat, energy-dense and make modest but important contributions to vitamin A, iron and zinc intake.

Together, these food supplements have the added plausible benefit of improving the microbiota and gut barrier function and reducing intestinal and systemic inflammation (figure 1). The IYCF-plus intervention will increase dietary diversity and micronutrient content, which has been shown to promote healthy gut microbiota composition.^31^ The resistant starch present in legumes is readily fermented by the gut microbiota to produce short-chain fatty acids, which act as a primary energy source for enterocytes, and other metabolites that maintain the integrity of the intestinal barrier.^32^ Recent trials suggest that legumes modestly improve linear growth and intestinal permeability^33 34^; these effects may be enhanced through integration with other micronutrients such as vitamin A and zinc, which can improve gut barrier function.^35 36^ Legume intake and high dietary quality scores have been associated with reduced systemic inflammation.^37^ Finally, preclinical studies have reported a role for moringa in reducing oxidative stress and improving immune function.^38^ We hypothesise that children receiving the IYCF-plus intervention will have a more mature microbiota, reduced EED, less systemic inflammation and an associated improvement in antipathogen immune cell function compared with the IYCF intervention.

Ultimately, through improved agriculture and animal husbandry practices families could become self-sufficient in producing the beans, biofortified maize, moringa and eggs used for the IYCF-plus intervention for their household. As these foods are already grown locally on a small scale, there is also potential for local commercial production and processing of these products that would allow public distribution or purchasing instead of direct household-level production. Furthermore, these inputs have useful synergies, for example, moringa pods and maize bran provide food for chickens that improves their feed efficiency and increases egg production.

## Formative research and community engagement

Formative work explored delivery and acceptability of the new food supplements proposed in CHAIN.^39^ Briefly, this qualitative study purposively sampled nine CHWs from the Shurugwi rural community where SHINE was conducted, in addition to 27 caregivers of children between 6 and 18 months of age. The aims of this formative work were to assess feasibility of delivering bean, egg and moringa powder to families; the acceptability of recipes devised to incorporate the new supplements into usual foods; and to inform IYCF-plus behavioural modules. The formative work also tested feasibility and uptake of this multicomponent complementary feeding and behaviour change strategy among similar rural households to the study setting.

Activities included focus group discussions with mothers, group-based recipe formulation, standardisation, testing and review as well as home visits to assess ingredient uptake, usage, storage and recipe adherence and innovations. Household observations and views from extended family members indicated high acceptability of the new ingredients. Sensory evaluation by mothers who formulated and standardised the recipes indicated high acceptability of the complementary food recipes. All formative study participants participated in developing the behaviour change messages and finalisation of the recipes in a recipe book developed for use in the CHAIN trial IYCF-plus intervention. The formative research demonstrated feasibility of implementing this multicomponent IYCF intervention comprising behaviour change counselling to promote optimal complementary feeding practices, building self-efficacy of caregivers through cooking demonstrations at home and provision and promoting use of nutrient-dense biofortified maize, moringa, NUA45 and egg powders to feed young children. Uptake of the multicomponent IYCF intervention was high. Household observations and sensory evaluation indicated high acceptability of the new food ingredients and multicomponent IYCF intervention.^39^

## Study setting and recruitment

The CHAIN trial was conducted in Shurugwi district, Zimbabwe. This is a predominantly rural, subsistence farming area, with 15% antenatal HIV prevalence and 35% stunting prevalence.^5^ CHWs are a community-level cadre of healthcare workers within the Ministry of Health and Child Care. All CHWs in the study area underwent a 2-week training on the interventions and have monthly supportive supervision meetings with study intervention nurses (INs). Additionally spot checks on performance are conducted. They sensitised community stakeholders and individual families in their catchment area between birth and 5 months of age about the CHAIN study and refer those who are interested to the trial team. A total of 282 infants turning 5 months of age from April 2021 to August 2021 were identified through CHW registers. Consent visits were scheduled as close as possible to children turning 5 months old, and continued until the required sample size was reached. All children who fulfilled the inclusion and exclusion criteria during enrolment were eligible for the trial, including households who had previously participated in the SHINE trial or the formative research with another child.

A research nurse visited the family’s homestead to screen the child for eligibility, provide information on the trial, and undertake written informed consent with the parent/legal guardian in Shona or Ndebele. If the caregiver was not available, visits were rescheduled. All household members were encouraged to be present for consent and subsequent intervention and research visits. Interventions, delivered by CHWs, started as soon as possible after randomisation, and the primary outcome is measured by research nurses at endline. Recruitment of study participants started on 26 April 2021 and study participants were followed until the end of February 2022.

## Trial outcomes

The primary outcome is energy intake in kcal at 9 months of age (visit window 9–11 months), as measured by multipass 24-hour dietary recall. Secondary and tertiary outcomes are defined in table 2.

**Table 2 T2:** Trial outcomes at 9 months of age (window 9–11 months)

Endpoint	Definition
Energy intake	Percentage of infants meeting daily energy requirements at 9 months of age (window 9–11 months), measured by multipass 24-hour dietary recall.
Protein, iron, zinc and folate intake	Percentage of infants meeting daily protein, iron, zinc and folate requirements at 9 months of age, measured by multipass 24-hour dietary recall.
Length-for-age Z-score	Length-for-age expressed as a Z-score compared with the WHO 2006 reference median
Weight-for-age Z score	Weight-for-age expressed as a Z-score compared with the WHO 2006 reference median
Weight-for-length Z score	Weight-for-length expressed as a Z-score compared with the WHO 2006 reference median
Haemoglobin	Concentration of haemoglobin (in g/dL) in a whole blood sample, measured by HemoCue point-of-care assay and adjusted for altitude
Microbiome maturity	Microbiota-for-age Z-score
Environmental enteric dysfunction	Biomarkers of intestinal inflammation (faecal neopterin and myeloperoxidase), small intestinal damage (plasma I-FABP and citrulline), intestinal permeability (faecal A1AT), microbial translocation (plasma sCD14, LBP), systemic inflammation (plasma CRP, AGP, TNF-alpha and K:T ratio) and growth hormone axis (IGF-1)
Innate immune cell phenotype	Surface marker expression by peripheral blood monocytes and neutrophils
Innate immune cell function	Surface marker expression and cytokine secretion from innate immune cells challenged with lipopolysaccharide in vitro relative to unstimulated controls Capacity of innate immune cells to internalise bacteria in vitro
Plasma essential amino acids	Plasma concentrations of phenylalanine, valine, threonine, tryptophan, methionine, leucine, isoleucine, lysine and histidine, as measured by LC-MS-MS
Plasma choline	Plasma concentration of choline, as measured by LC-MS-MS
Urinary metabolic signature	Global untargeted metabolomic phenotyping undertaken by ^1^H nuclear MR spectroscopy

AGP, alpha-1 acid glycoprotein; CRP, C reactive protein; LBP, lipopolysaccharide binding protein; LC-MS-MS, liquid chromatography-mass spectrometry.

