## Sample size

The sample size of 192 infants assumes 10% lost to follow-up due to withdrawal and infant deaths, meaning there will be an estimated 86 evaluable infants per group at endline. This sample size provides 86% power at 5% significance to detect a 20% increase in the proportion of infants achieving their recommended energy intake (by 24-hour dietary recall) in the IYCF-plus arm, assuming that only 65% of infants are meeting requirements in the IYCF (standard-of-care) arm based on SHINE data. If lost to follow-up is as high as 15%, we will still have 80% power to detect a 20% increase in the proportion reaching their daily energy intake (study primary outcome).

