The primary outcome, percentage of infants meeting energy intake (kcal/day), will be calculated using measured intake data from dietary recalls from all participants. Dietary energy intake (DEI) was collected through an interactive, multiple-pass, 24-hour recall at the 9-month endpoint among all children, and in 50% of children through an additional dietary recall 7 days later. The DEI estimate will be used with a logistic regression model clustering for the repeat measure using the multilevel mixed-effects logistic regression method. This method will be implemented within STATA. It is well recognised that the dietary intake data contain a lot of uncertainty, and thus, we will conduct a sensitivity analysis using the National Cancer Institute (NCI) method calculated for usual overall average intake. We will estimate the mean and percentiles of usual energy intake distributions using the NCI method.^53 54^ This method adjusts for measurement error—primarily due to day-to-day variability in intakes—in observed, single-day estimates of nutrient intakes. We will use the NCI macros, DISTRIB and MIXTRAN, plus bootstrapped SEs for hypothesis testing.^25 27^ The MIXTRAN macro fits a mixed effects model of usual energy intake, and the DISTRIB macro uses a Monte Carlo procedure to estimate percentiles of the usual intake distribution. We will use the MIXTRAN macro to fit a model of energy intake with a fixed effect for intervention group and the DISTRIB macro to estimate usual energy intake distributions by treatment group. We will bootstrap the parameters to estimate the SE of the mean usual intakes. We will use the point estimates and SE estimates to construct 95% CIs and calculate p values for difference in mean by intervention group based on Welch’s t-test. Bootstrapped SEs will be calculated using bootstrap samples. When intake or the number of repeat recalls is low, it is common for the NCI method to fail to converge. In cases where convergence prohibits bootstrapping, we will test hypotheses using the Wilcoxon testing for clustered method.

We will also interpret the mean intake of each nutrient for the primary and secondary analysis in each arm and will present mean differences with the 95% CI for interpretation.

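### The single primary outcome is defined both as energy intake in kcal and as the percentage of infants meeting their energy requirement, so the confirmatory test is not fixed

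*Protocol article*

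**What the plan says.** Continuous definition, with no threshold:

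- Abstract, Methods and analysis: "The primary outcome is energy intake, measured by multipass 24-hour dietary recall at 9–11 months of age".
- Study overview: the primary endline outcome is energy intake.
- Objective 1: the supplements "will provide more energy at 9 months of age than the current standard-of-care IYCF intervention (trial primary outcome").
- Trial outcomes, opening sentence: "The primary outcome is energy intake in kcal at 9 months of age".

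Binary definition:

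- Sample size: the 86% power is for a rise from 65% in the proportion of infants achieving the recommended intake. The section then refers to power "to detect a 20% increase in the proportion reaching their daily energy intake (study primary outcome").
- Statistical analysis: "The primary outcome, percentage of infants meeting energy intake (kcal/day), will be calculated using measured intake data from dietary recalls from all participants". The model assigned to it is a multilevel mixed-effects logistic regression that accounts for the repeat recall.

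Table 2 is introduced as defining the secondary and tertiary outcomes. Its first row, labelled energy intake, reads "Percentage of infants meeting daily energy requirements at 9 months of age (window 9–11 months").

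A sensitivity analysis by the NCI method follows. It estimates the mean and percentiles of usual intake by arm. The hypothesis test described for it is on the mean: "We will use the point estimates and SE estimates to construct 95% CIs and calculate p values for difference in mean by intervention group". Mean differences with 95% CIs will also be presented for interpretation. Two-sided p<0.05 counts as significant throughout.

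**The concern.** An article may leave model details to the analysis plan. Here, though, it states the primary outcome itself in two ways that cannot both be right. Mean kcal and the percentage above a requirement are different quantities, with different tests and different effect measures.

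Both comparisons are planned, each yields a p value, and no rule says which governs if they disagree. A significant mean difference could be presented as primary by citing Trial outcomes. A significant odds ratio could be presented as primary by citing Sample size and Statistical analysis. That opens the way to choosing the outcome after the results are known.

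The sensitivity analysis is affected too. Its stated purpose is to deal with day-to-day error in one-day recalls. A test on mean usual intake cannot show whether the result on the percentage survives that correction.

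**Working it through.** **1. The definitions side by side**

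| Place in the protocol article | Definition | Role given |
|---|---|---|
| Abstract; Study overview | energy intake, no threshold | primary |
| Objective 1 | more energy, no threshold | primary |
| Trial outcomes, text | kcal | primary |
| Trial outcomes, Table 2, first row | percentage meeting requirement | secondary or tertiary, by the table's introduction |
| Sample size | proportion reaching requirement | primary |
| Statistical analysis, main model | percentage meeting requirement (logistic) | primary |
| Statistical analysis, NCI test | mean usual kcal | sensitivity |

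Table 2 does not settle the matter. If its first row is secondary, it conflicts with Sample size and Statistical analysis. If that row is the primary outcome, it conflicts with the sentence that opens its own section.

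**2. The stated power, reproduced**

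Inputs from Sample size: 192 infants, 10% loss, 65% in the control arm, a 20% increase, 5% significance. Statistical analysis makes tests two-sided.

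- Evaluable per arm: 192 × 0.9 / 2 = 86.4, so 86.
- The 20% is read as percentage points, 65% to 85%. Pooled-variance normal approximation:
  - SE under the null = √(2 × 0.75 × 0.25 / 86) = 0.0660
  - SE under the alternative = √((0.65 × 0.35 + 0.85 × 0.15) / 86) = 0.0642
  - Power = Φ((0.20 − 1.96 × 0.0660) / 0.0642) = Φ(1.098) = 86.4%
- A relative 20% increase (65% to 78%) would give only 47%, which confirms the reading.

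The 86% is therefore correct, and it is the power for the percentage. No power is stated for kcal.

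**3. The same effect on the kcal scale**

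Assumptions, not from the article: intake is normal with equal SD in both arms, and one cut-off applies to all infants.

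- Shift: d = z(0.85) − z(0.65) = 1.036 − 0.385 = 0.651 SD.
- Noncentrality with 86 per arm: 0.651 × √(86/2) = 4.27.
- Power = Φ(4.27 − 1.96) = 99.0%. The noncentral t gives 98.9%.
- For 86% power, kcal needs about 45 per arm (noncentral t; 44 gives 85.5%). The percentage needs 85 per arm, about 1.9 times as many.

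**4. Information kept after dichotomising**

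Under the same model, the fraction kept is φ(z_p)² / (p(1 − p)):

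| p | Kept | Lost |
|---|---|---|
| 0.65 | 60% | 40% |
| 0.75 | 54% | 46% |
| 0.85 | 43% | 57% |

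Roughly half is lost.

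**The case against.** **Roles are assigned.** Statistical analysis makes the logistic model the main analysis, labels the NCI analysis as sensitivity, and offers mean differences for interpretation. A reader might infer two co-primary outcomes, each tested at 5%. The text does not support that: it declares no co-primary tests. It gives one primary outcome two definitions. The roles within Statistical analysis do not remove the conflict with Trial outcomes, Objective 1 and the abstract.

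**The percentage is a defensible outcome.** It matches the aim of closing nutrient gaps, and the stated 86% power for it reproduces. A reader might infer that the trial is underpowered, or that dichotomising throws away most of the information. Neither is supported. On its own assumptions the trial is adequately powered for the percentage, and the loss is about 40% to 57%.

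**The kcal power figures are illustrative.** The article gives no SD for energy intake. It also sets the energy requirement per kilogram of body weight (Follow-up data collection), so the percentage is not a pure cut of kcal. This stands. It is also tempting to calculate power from the 129 kcal supply contrast in Table 1 (247 − 118 at 9–11 months). Such figures would depend mainly on the SD chosen. They would also sit badly with the 65% control rate, because Table 1 puts the control total, 368 kcal, below the 451 kcal requirement. They are not relied on here.

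**The NCI analysis also estimates percentiles of usual intake by arm.** That is related to meeting a requirement, but the only test stated is on the mean.

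**Conclusion.** The contradiction is in the text and needs no assumption. The primary outcome is kcal, or energy intake without a threshold, in four places. It is the percentage meeting the requirement in the two sections that set the sample size and the main model. Table 2 adds to the conflict. Until this is resolved, the confirmatory test is undetermined, and the sensitivity analysis does not test the binary result.

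The two definitions are not interchangeable in efficiency: about 99% against 86% power at 86 per arm for the same underlying shift. That comparison rests on normality, equal SDs and one common cut-off. It supports preferring kcal but does not show that the percentage is an invalid choice. The need to settle on one definition does not depend on it.

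**What to change.** Before any comparison by arm, name one primary outcome. Align the abstract, Study overview, Objective 1, Trial outcomes, Table 2, Sample size and Statistical analysis to it, and make the other version a named secondary outcome.

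**Preferred: mean energy intake in kcal/day.** It agrees with the abstract, Study overview, Objective 1 and Trial outcomes. Analyse it with a linear mixed model that uses both recalls (arm effect, random intercept for child), and report the mean difference with its 95% CI. The NCI comparison of means then becomes a true sensitivity analysis. The percentage of infants individually classified as meeting their requirement becomes secondary, and the 86% power applies only to that comparison. A power statement for kcal would need an SD with a stated source.

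**Alternative: keep the percentage.** Correct the abstract, Study overview, Objective 1, Trial outcomes and the status of Table 2's first row. Add an NCI comparison by arm of the proportion meeting the requirement as the sensitivity analysis. The power statement and main model can then stay.

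Either route costs wording and an entry in the analysis plan, which the article says will be posted before analyses begin. No new data are needed, although data collection is complete, so the choice should be documented as made before the arms were compared. The cost of the preferred route is that meeting requirements is no longer the headline result.
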